**Figure 1 F1:**
[figure not shown]
**Study Design**. Patients are randomly allocated to either the preemptive or the postoperative treatment group. Preemptive group patients get etoricoxib 120 mg p.o. prior to surgery (day 0, preoperative). After surgical intervention, depending on their respective allocation, patients receive either etoricoxib 120 mg p.o. or placebo for the next three postoperative days (day 1-2-3, postoperative). Postoperative group patients get placebo prior to surgery and continue afterwards with either placebo or etoricoxib 120 mg p.o. for three postoperative days (2 × 2 factorial study design). The listed outcome measures will be assessed at the marked time points respectively.

We conducted a 2 × 2 factorial-armed study which should prove the superiority of preemptive versus postoperative etoricoxib. The study was based on the moderate effective size of pre-emptive etoricoxib vs. post-operative etoricoxib in the reduction of the 48 hour cumulative morphine consumption. A sample size of approximately 60 patients in the two arms (i.e. 30 patients in each of the four arms) is anticipated taking a drop out rate of 10% into account (this is a conservative estimate based on the dropped out rate of 4% in the study by Sinatra et al. [19]). With this sample size we would permit a type I error of alpha = .05, and with the alternate hypothesis, the null hypothesis would be retained with a type II error of beta = .2 (i.e. power of 80%).

The calculation of the effective size is based on the data of Sinatra et al. [19]. The authors found a mean reduction of cumulative morphine consumption of 23 mg in the treatment group (total morphine dose 45 mg, SD 14) compared to the placebo group (total morphine dose 68 mg, SD 25).

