#### Secondary outcome measure

- Baseline personal situation on the DGSS (German Society for the Study of Pain) validated pain questionnaire [24], comprising inter alia the German versions of questionnaires assessing demographic data, pain variables (e. g. pain sites, temporal characteristics, duration, intensity), pain associated symptoms, affective and sensory qualities of pain (adjective list by Geissner, SES), pain relieving and intensifying factors, previous pain treatment procedures, pain-related disability (Pain Disability Index), depression (Centre for Epidemiological Studies Depression Test CES-D), comorbid conditions, social factors (educational level, occupation, retirement status, compensation or litigation status, disability for work), health related quality of life (SF-36).

- Systematic quantitative sensory testing (QST). The detailed QST protocol including reference data is reported elsewhere [25]. In brief, the following testing procedures were performed:

a) **Thermal Testing **comprising cold and warm detection thresholds (CDT, WDT), paradoxical heat sensations (PHS) during the thermal sensory limen procedure (TSL) of alternating warm and cold stimuli and cold and heat pain thresholds (CPT, HPT);

b) **Mechanical Testing **comprising mechanical detection thresholds (MDT), mechanical pain thresholds (MPT), mechanical pain sensitivity (MPS), dynamic mechanical allodynia (DMA), the wind-up ratio (WUR), vibration detection thresholds (VDT) and pressure pain thresholds (PPT).

- Pain intensity (visual analogue scale)

- Overall morphine consumption

- Side effects (documentation according to ICH - GCP Guidelines)

- Genetic polymorphisms: the metabolic profile of etoricoxib involves cytochrome P450-dependent hydroxylation and oxidation as primary clearance pathways [26]. Different genotypes might either be the reason for individually different analgesic needs or be considered as a risk factor for side effects [27]. Similar mechanisms have been described for the use of opioids and so called multidrug resistance proteins (MDR) [28]. We therefore collected EDTA-blood samples from all patients to analyse the different expression of genotypes.

For time points please refer to Figure 1.

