### Data Analysis

Descriptive analysis of the study population (including means, standard deviations, median and frequencies) will be made for all parameters.

Main outcome measures will be analysed with a 2 × 2 factorial ANOVA. Independent variables are time point of medication uptake and allocated study arm, dependent variable is the cumulative morphine consumption within 48 hours postoperatively.

Secondary outcome measures (QST, pain intensity) will be analysed equivalent, taking into account the test interval (repeated measurement ANOVA). ANOVA will be adjusted according to Bonferroni using t-test for post-hoc confirmation of significant alterations.

Ordinal scaled data will be analysed with Kruskal Wallis test confirming significance with chi2 test.

For analyses of associative coherence we will use Spearman's correlations coefficient, Wilcoxon-test or Kruskal Wallis test. All reports will be performed according intention-to treat analysis.

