### Data entry

Data entry is done with SPSS statistical software system (SPSS Inc., Chicago, IL; version 15.0). Data analysis will be done with SAS/STAT^® ^Software (SAS Institute Inc., Cary, NC, USA). All data entry will be carried out twice.

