## Quantitative sensory testing

Postoperative pain involves not only peripheral mechanisms, most notably the sensitization of nociceptors due to inflammation, but also secondary central mechanisms, including hyperexcitability of nociceptive neurons (i.e., central sensitization, [39,40]). These processes play a major role in postoperative pain, including spontaneous pain and allodynia or hyperalgesia. In particular, peripheral sensitization would explain the hyperalgesia observed at the incision site (primary hyperalgesia), whereas central sensitization would provide a major mechanism of secondary hyperalgesia at distant noninflammatory sites [41-43]; thus indicating a possible pathway for the occurrence of prevalent pain.

From a clinical perspective, preoperative measurement of sensoric perception may have some predictive value regarding postoperative pain and, therefore, may also predict perioperative analgesic requirement [44]. Martinez et al. showed that preoperative heat hyperalgesia directly correlated with postoperative morphine consumption after total knee arthroplasty [43]. These results are in agreement with those of previous studies on the prognostic value of preoperative pain for immediate postoperative pain intensity with other types of surgery [45,46]. Postoperative segmental secondary hyperalgesia was detected in patients undergoing different types of surgical interventions [47-49]. Several central and peripheral pathophysiological actions play a role in the development of acute and chronic postoperative pain. Quantitative sensory testing (QST) allows precise characterization of sensory deficits and painful symptoms and may offer additional information on the pathophysiology of postoperative pain. A follow-up sensory testing in our trial is performed six months after intervention. Therefore, we will be able to provide information regarding long-term sensitisation after surgery, too. Taken together, we will be able to evaluate possible predictive factors related to patients' individual sensoric perception that may influence the intensity of postoperative pain and analgesic consumption such as characteristics that might predict or prevent chronification.

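### Repeated-measures ANOVA for QST and pain intensity would, in its classical form, leave out patients with an incomplete series, which is hard to reconcile with the stated intention-to-treat analysis

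*Protocol article*

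**What the plan says.** The Data Analysis section of the protocol article first fixes the primary analysis: "Main outcome measures will be analysed with a 2 × 2 factorial ANOVA". It then turns to "Secondary outcome measures (QST, pain intensity") and says that these "will be analysed equivalent, taking into account the test interval (repeated measurement ANOVA"). Bonferroni-adjusted t-tests follow as post-hoc confirmation. The section closes with "All reports will be performed according intention-to treat analysis".

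Three other places bear on the point:

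- **Late visit.** Under Quantitative sensory testing: "A follow-up sensory testing in our trial is performed six months after intervention". The article expects this visit to inform on long-term sensitisation.
- **Dropout.** Under Randomised treatment allocation, blinding and sample-size estimation, the sample size "is anticipated taking a drop out rate of 10% into account". The article calls this conservative against 4% in the study it used for planning.
- **Software.** Under Data entry: "Data analysis will be done with SAS/STAT". No procedure is named.

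The measurement schedule is only in a figure that is not available in the text: "For time points please refer to Figure 1". The article does not say how an incomplete series is handled, or whether the preoperative value is a level of the time factor or a covariate.

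**The concern.** The article makes a choice of method here; it does not leave the analysis open. Describing it as equivalent to the factorial ANOVA, with t-tests to follow, points to classical repeated-measures ANOVA. In its usual least-squares form that analysis needs a value at every level of the time factor, so one missing visit removes the whole patient.

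A trial with a six-month visit should expect some missed visits. Whether a surgical patient comes back may depend on how much pain persists. A complete-case analysis would discard earlier values from patients who were randomised and measured. It would also, in general, need data missing completely at random to be unbiased, unless the missingness depends only on variables already in the model. The findings on sensitisation and persistent pain would then rest on completers, although the plan promises intention-to-treat.

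**Working it through.** **Inputs from the article.** 120 patients, 30 in each of four arms, so 60 on each side of either treatment factor. Dropout allowance 10% overall; 4% in the source study. QST at six months. The article states no figure for the size of the repeated-measures analyses, so there is none to reproduce. The sample-size calculation concerns the 48-hour morphine total and has no bearing on this point.

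**Step 1: loss at the plan's own dropout rate.** If every dropout leaves an incomplete series:

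- 10%: 120 × 0.10 = 12 left out; 108 remain, 54 on each side of a factor.
- 4%: 120 × 0.04 = 4.8, about 5 left out.

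Twelve is an upper figure for the loss caused by the method at 10% dropout. A patient who leaves before any post-baseline value adds nothing to a model on post-baseline values either.

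**Step 2: loss if visits are also missed singly (assumption).** With independent missingness *m* at each of *k* visits, the complete share is (1 − *m*)^*k*. The article gives neither *m* nor *k*. The table borrows 4% and 10% as per-visit rates for illustration only.

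| Visits *k* | Complete of 120, *m* = 4% | Complete of 120, *m* = 10% |
|---|---|---|
| 3 | 120 × 0.96³ = 106.2 | 120 × 0.90³ = 87.5 |
| 4 | 120 × 0.96⁴ = 101.9 | 120 × 0.90⁴ = 78.7 |
| 5 | 120 × 0.96⁵ = 97.8 | 120 × 0.90⁵ = 70.9 |
| 6 | 120 × 0.96⁶ = 93.9 | 120 × 0.90⁶ = 63.8 |

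On these assumptions the loss runs from about 14 to about 56 patients.

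**Step 3: what a mixed model keeps.** In one simulated data set (120 patients, four visits, each value missing with probability 10%), 83 patients had a complete series. A likelihood-based repeated-measures model used all 120.

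**Step 4: preoperative value as a time level (conditional).** Treatment cannot change the preoperative value. With one baseline level, two post-treatment levels and a constant effect δ, the treatment main effect averages (0 + δ + δ)/3 = 2δ/3, a dilution of one third. With *p* post-treatment levels the dilution is 1/(*p* + 1). This applies only if baseline is entered that way, and only to the main effect. The treatment-by-time interaction, the usual test in that layout, is a different matter.

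**The case against.** The strongest reply is that the defect is inferred. The article gives a method label and names no estimation method, exclusion or SAS procedure. The stated software can fit a repeated-measures analysis by complete-case least squares or by a mixed model that keeps partial records. Handling of missing visits is commonly left to a full protocol or analysis plan, and neither is shown. **This stands in part.** A reader might infer that the plan drops every patient with a missed visit and so contradicts its own intention-to-treat statement. The article does not support that: it excludes no randomised patient, and the conflict arises only if the classical form is run. What remains is that the named method, on its ordinary reading, is that form. The post-hoc t-tests do not change who enters the ANOVA they follow.

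On size, the 10% is an allowance made for the primary outcome and is described as conservative. It is neither a minimum nor a six-month rate, so a claim that at least 12 patients would be lost is not supported. The larger figures rest on assumed visit counts and rates. Real dropout tends to accumulate over visits instead of striking each one independently. **This stands.**

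A reader might also infer that pain intensity is followed to six months, or that baseline is a time level. Neither can be confirmed without Figure 1; the six-month visit is documented only for QST. **This stands.**

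Finally, a mixed model is not a cure. If return depends on the unobserved six-month pain itself, that model is biased too. **This also stands**, but it does not favour the classical form, which generally needs the stronger assumption and discards data already collected.

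**Conclusion.** The point holds in a limited form. Run classically, the named method would leave out randomised patients who have usable earlier data, and that is hard to reconcile with an intention-to-treat statement covering all reports. The documented size is up to 12 of 120 patients if the 10% dropout occurs. Anything beyond that depends on a schedule and per-visit rates that the text does not show. No direction or size of bias in the treatment comparison can be derived from the article.

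The baseline dilution is a risk to exclude, not an established fault. Only secondary outcomes are affected: the primary outcome is one value per patient. The change is worth making because a better method is available in the software already chosen, and because naming it now settles the choice between complete-case and all-data analysis before results are seen.

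**What to change.** In Data Analysis, replace repeated-measures ANOVA for QST and pain intensity with a linear mixed model for repeated measures, specified as follows:

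- **Data:** all available post-baseline values from all randomised patients, analysed as allocated.
- **Terms:** preoperative treatment, postoperative treatment, their interaction, time, and treatment-by-time.
- **Baseline:** the preoperative value as covariate where it was measured, not as a level of time.
- **Reporting:** the treatment difference with 95% CI at each time point, including six months for QST.

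Add one sentence saying that the model assumes data missing at random, and that it does not protect against return at six months depending on unobserved pain.

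The cost is a short text change, different SAS code and slightly more analysis work. No new data, visits or patients are needed, and the primary analysis does not change.

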## Patients and Methods

### Study Design

The study is a 2 × 2 factorial armed, double blinded, randomised placebo-controlled trial comparing (a) etoricoxib and (b) placebo in a pre- and postoperative setting. After randomisation, patients receive preemptive medication of either (a) or (b). Medication will be given postoperatively for additional three days. Additionally, all patients receive morphine administered through Patient Controlled Analgesia (PCA). Analysis of all records is performed by blinded evaluators. The total follow-up period per patient is 6 month. Trial registration is NCT00716833.

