## Study Design

We have chosen a 2 × 2 factorial design for the following reasons: the factorial design has several important features. Firstly, it has great flexibility for exploring the treatment effects in the trials. Whenever examining treatment variations, factorial designs are strong candidates as the design of choice. Secondly, factorial designs are efficient due to the ability to combine multiple studies into one rather than conducting a series of independent studies. Finally, factorial designs are the only effective way to examine interaction effects [53,54].

If the primary aim of a trial is to identify useful single treatments, then it could possibly be more cost effective to use a three-arm study than a 2 × 2 factorial design. In this trial, it is of interest to detect the treatment interaction, i.e. the opioid-sparing effect of a non-opioid treatment. The chosen study design has the power to identify such statistically significant differences between etoricoxibe and placebo treatments [55]. While the methods are developed for binary outcomes, they can be readily adapted to outcomes based on continuous, ordinal or time-to-event data using the methods for power calculation [55,56]. No attempt has been made to adjust for multiple comparisons. However, this can be achieved by simply changing the level of significance according to some recognised procedures such as the Bonferroni correction [55,57]. In our opinion, the study design allows to obtain specific results regarding the preemptive and postoperative analgesic effects of etoricoxib on (a) the cumulative morphine consumption and (b) other parameters as mentioned: predisposing characteristics influencing postoperative pain (inter alia by means of questionnaires), sensoric perception, genetic polymorphisms and others.

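### Ordinal data: a chi-square test cannot confirm a Kruskal-Wallis result, and a four-arm Kruskal-Wallis does not separate the two factors

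*Protocol article*

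**What the plan says.** The Data Analysis section of the protocol article gives one rule for ordinal data: "Ordinal scaled data will be analysed with Kruskal Wallis test confirming significance with chi2 test". It does not state which groups are compared, or what follows if the two tests disagree.

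The other outcomes are treated differently. In the same section, "Main outcome measures will be analysed with a 2 × 2 factorial ANOVA", and quantitative sensory testing (QST) and pain intensity are handled in the same way with repeated measurements added.

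The design is factorial: "The study is a 2 × 2 factorial armed, double blinded, randomised placebo-controlled trial". The later Study Design section, which follows Genetics, gives several reasons for that choice. One is that "factorial designs are efficient due to the ability to combine multiple studies into one". Another is the ability to examine interaction, and it adds: "In this trial, it is of interest to detect the treatment interaction".

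**The concern.** There are two separate weaknesses.

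1. **The confirming step.** Kruskal-Wallis works on ranks and so uses the ordering of the categories. A Pearson chi-square test treats the categories as nominal labels. Applied to the same patients, it is not independent evidence, and against a shift along the scale it is the less sensitive test. If it disagrees with a significant rank test, the likely reason is its lower power. As a second hurdle, it makes the procedure conservative.

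2. **The factors.** Kruskal-Wallis is a one-way test. Over four arms it asks whether any arm differs from any other. It cannot say whether the preoperative or the postoperative tablet is responsible, cannot test the interaction that the article calls of interest, and gives no effect estimate for either factor. Ordinal data would then be the only treatment comparison in the plan that leaves the factorial structure.

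At stake are the sensitivity and the interpretability of the ordinal secondary results.

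**Working it through.** The article gives no figure for ordinal outcomes, so there is none to reproduce. What follows measures the stated procedure against a factor-specific rank test.

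**Inputs from the article.** The planned size is: "A sample size of approximately 60 patients in the two arms (i.e. 30 patients in each of the four arms) is anticipated". That figure already allows for 10% dropout. Evaluable patients per arm: 30 × 0.9 = 27. Alpha is 0.05, taken as two-sided because the side is not stated.

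**Assumptions, because the article gives none.** Four-arm grouping, a proportional-odds shift, the category distributions, and the size of the effect.

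**Degrees of freedom.** Kruskal-Wallis over 4 arms: 4 − 1 = 3. Pearson chi-square, 4 arms by K categories: 3 × (K − 1), which is 6, 9 and 12 for K = 3, 4 and 5.

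**Analytic check.** A 1-df test has 80% power at noncentrality (1.960 + 0.842)² ≈ 7.85. The same noncentrality gives:

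| df | Power |
|---|---|
| 1 (factor test) | 80% |
| 3 (Kruskal-Wallis, 4 arms) | 64% |
| 6 (chi-square, 3 categories) | 52% |
| 9 (chi-square, 4 categories) | 45% |
| 12 (chi-square, 5 categories) | 39% |

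**Simulation, preoperative effect only, odds ratio 2.5.** 27 per arm, 2,000 trials per row, Monte Carlo standard error about 1 point. The stratified Wilcoxon (van Elteren) tests the preoperative factor within levels of the postoperative factor.

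| Categories | Stratified Wilcoxon | Kruskal-Wallis, 4 arms | Chi-square, 4 arms | Both significant |
|---|---|---|---|---|
| 3 equal | 72.0% | 55.0% | 43.8% | 40.2% |
| 4 equal | 72.8% | 54.1% | 36.2% | 32.5% |
| 5 equal | 73.0% | 55.4% | 29.4% | 26.4% |
| 11 equal | 77.4% | 61.1% | 19.2% | 16.9% |
| 4 skewed (50/25/15/10) | 64.4% | 48.1% | 29.6% | 26.3% |

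- Cost of the omnibus test alone: from 64.4 − 48.1 = 16.3 to 72.8 − 54.1 = 18.7 points. At odds ratio 3 it is 12.6 to 15.6 points.
- Further cost if chi-square must agree: from 55.0 − 40.2 = 14.8 to 61.1 − 16.9 = 44.2 points. At odds ratio 3 it is 15.6 to 49.9 points.

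**A second setting.** Five categories cut at −0.8, −0.2, 0.4 and 1.0 on a logistic scale with SD 1, preoperative shift 0.5 SD. This corresponds to an odds ratio of exp(0.5 × π/√3) = exp(0.907) ≈ 2.5. Kruskal-Wallis has about 56% power, chi-square 32%, and both together 29%; a Wilcoxon test of the factor has 74%. Repeat runs agree within simulation error.

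**No effect at all.** Over the five category sets, Kruskal-Wallis alone rejects in 3.6–5.0% of trials. Both tests together reject in 0.6–2.4%.

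**Both factors active, odds ratio 2 each.** Kruskal-Wallis 49–65%, the stratified test of one factor 39–53%, both tests required 19–42%. In the five-category setting, adding a postoperative effect of 0.25 SD gives Kruskal-Wallis 68% against 74% for the factor test. Adding 0.5 SD gives 87% against 70%.

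**The case against.** **The grouping is inferred.** The sentence names no groups. If Kruskal-Wallis were applied to the two levels of each factor, it would be a 1-df rank test and the 3-df criticism would fall away. That stands as a condition. Four arms remain the natural reading, since the test is ordinarily chosen for three or more groups. The chi-square step is weak on the two-level reading too. At odds ratio 2.5, a two-group chi-square on the preoperative factor has 36–63% power over the five category sets, against 64–77% for the stratified Wilcoxon.

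**The joint rule is inferred.** The article does not say that both tests must be significant, and the term could conceivably mean the chi-square reference distribution of the Kruskal-Wallis statistic. The wording reads more naturally as a second test, but the 29% figure holds only under a joint rule. Without one, the loss is at most that of 3 df against 1 df.

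**The omnibus test is not always weaker.** This is correct. When both factors act with similar strength it has more power than a test of one factor, because it asks a broader question. It still does not say which factor acted.

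**Scope.** No ordinal outcome is named as such or powered, and the main outcomes are analysed by ANOVA. This keeps the point minor. Listing the ordinal outcomes may well be left to a fuller document. The choice of test and the confirming step, however, are fixed here.

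**Conclusion.** The point holds as a minor one. The chi-square confirmation adds no evidence. Under a both-significant rule it is conservative, with type I error of about 0.6–2.4%, and it takes about 15 to 50 points of power from Kruskal-Wallis when one factor acts. A four-arm Kruskal-Wallis cannot attribute an effect to a factor or test the interaction. When one factor acts it loses about 13 to 19 points against a factor-specific rank test (80% to 64% analytically). The sizes rest on the assumed category distributions, effects and grouping. The argument about ordering and about the factors does not depend on the effect size.

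Three stronger readings are not supported:
- **That the whole ordinal procedure ignores ordering.** Kruskal-Wallis uses ranks; only the chi-square step discards the order.
- **That the procedure raises the false-positive rate.** Confirming a significant result can only lower it. Nothing in the text suggests accepting either test alone.
- **That the trial as a whole loses the efficiency of its factorial design.** The primary outcome keeps a factorial ANOVA, and efficiency is only one of the reasons given for the design.

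**What to change.** In Data Analysis, replace the sentence on ordinal data:

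- Delete the chi-square confirmation and keep chi-square for nominal data.
- Analyse ordinal outcomes with a proportional-odds model containing preoperative treatment, postoperative treatment and their interaction. Report odds ratios with 95% confidence intervals. Code the factors as ±½ so that each factor's odds ratio averages over the other on the log-odds scale.
- Alternatively, use a Wilcoxon test of each factor stratified by the other (van Elteren).

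The cost is one sentence and standard code in the planned SAS software, with no extra patients or data. The model assumes proportional odds. The stratified Wilcoxon avoids that assumption but does not test the interaction. The interaction will be imprecise either way: for a simple difference, its variance relative to a main effect is (4/27) ÷ (2/54) = 4, so its standard error is about twice as large. It is best reported as an estimate with its interval.

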## Genetics

Genetic polymorphisms in P-glycoprotein (P-gp), a membrane-localised transporter codified by the gene MDR1 and Cytochrome P450 (CYP) genes, are involved in drug metabolism and often account for variable drug response or side effects. Some common drugs, including non-steroidal anti-inflammatory drugs, are metabolised by the P450 CYP2 C9 enzyme. There are mostly three variants of CYP2C9 gene which show alternated drug response. The variants *CYP2C9*1*, **2 *and **3 *occur most frequently with those of a caucasian background [50]. The enzymatic activity of **2 *and **3 *variant genes is decreased significantly, and carriers of the *3 variant are at risk for complications, such as bleeding after use of warfarin in small amounts [51]. Newer COX-2 inhibitors have less potential for causing gastrointestinal bleeding. The COX2 inhibitor etoricoxib has plasma protein binding of about 92% and is extensively metabolised, with only about 1% being excreted in urine as parent drug. CYP3A4 plays a major role in the metabolism of etoricoxib (60%), and CYP2C9, CYP2C19, CYP2D6 account for only a minor fraction ( 10%) of etoricoxib's metabolic profile [52]. Even though the pharmacokinetic profile is linear and in vitro studies support that etoricoxib does minor induction or inhibition of CYP isoenzymes, we want to test whether the mentioned CYPs or the polymorphisms of the MDR1 (e.g. C3435T) have a possible connection with the outcome of postoperative pain management.

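### The tests named for associations carry no term for randomised arm: some power is lost for baseline predictors, false links can arise between postoperative measures, and an etoricoxib-mediated CYP effect is diluted

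*Protocol article*

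**What the plan says.** The Data Analysis section treats two kinds of question differently. For treatment comparisons, 48-hour morphine use goes into a 2 × 2 factorial ANOVA, and the longitudinal measures follow the same model: "Secondary outcome measures (QST, pain intensity) will be analysed equivalent, taking into account the test interval (repeated measurement ANOVA"). Treatment is in both models.

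For associations the section has one sentence: "For analyses of associative coherence we will use Spearman's correlations coefficient, Wilcoxon-test or Kruskal Wallis test". It names no variable pairs, no analysis population and no stratification.

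Other sections supply the questions that this sentence would serve:

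- Quantitative sensory testing: "we will be able to evaluate possible predictive factors related to patients' individual sensoric perception that may influence the intensity of postoperative pain", together with analgesic consumption. The same section adds that "A follow-up sensory testing in our trial is performed six months after intervention".
- Genetics: the aim is to test whether the listed CYPs or "polymorphisms of the MDR1 (e.g. C3435T) have a possible connection with the outcome of postoperative pain management".
- Secondary outcome measure: the CYP rationale is that "the metabolic profile of etoricoxib involves cytochrome P450-dependent hydroxylation and oxidation as primary clearance pathways". Blood is taken from all patients.
- Conclusion: sensory perception and genetic predisposition appear again as expected results.

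Under Interventions, one of the four arms receives placebo both before and after surgery.

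**The concern.** The outcome in these associations, morphine use or pain, is the one that the trial sets out to change by randomised treatment. Spearman, Wilcoxon and Kruskal-Wallis tests in their ordinary form ignore that structure. What this does depends on the type of variable:

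1. **Measured before treatment (baseline sensory tests, genotype).** Randomisation makes these independent of arm in expectation. Differences between arms in morphine use only add noise.
2. **Measured after treatment (later sensory tests, pain scores).** If etoricoxib shifts both variables, pooling over arms produces a correlation even when no patient-level link exists within any arm. A treatment effect could then be read as a link between sensitisation and pain.
3. **CYP genotype.** An effect through etoricoxib clearance can exist only in patients who take etoricoxib. A test over all patients averages it with zero in the placebo/placebo arm, and cannot tell a drug-metabolism effect from a general one.

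**Working it through.** **Inputs from the article** (section on allocation, blinding and sample size): 30 patients per arm, four arms, 10% dropout, alpha 0.05; cited source data of 45 mg (SD 14) on treatment and 68 mg (SD 25) on placebo. The article gives no power or precision figure for associations, so there is none to reproduce. Its sample size is used here only for the number analysed: 120 × 0.9 = 108, or 27 per arm.

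**Assumptions, not in the article:** within-arm correlation 0.3; the pattern of arm effects; shifts in postoperative measures; carrier share and CYP effect. Tests are two-sided at 5%.

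**Step 1. How much of morphine variance is arm?** Put the placebo/placebo arm at 68 mg and the three active arms at 45 mg. The grand mean is (68 + 3 × 45)/4 = 50.75.

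- Between arms: (17.25² + 3 × 5.75²)/4 = 99.2
- Within arms: (25² + 3 × 14²)/4 = 303.25
- Share due to arm: 99.2/(99.2 + 303.25) = 25%

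**Step 2. Scenarios in SD units.** The pooled SD is √((14² + 25²)/2) = 20.3, so the cited effect is 23/20.3 = 1.135 SD. The trial's own target is described only as moderate, taken here as 0.5 SD. With within-arm variance 1, let V be the variance of the four arm means, in the order placebo/placebo, postoperative only, preoperative only, both:

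| Scenario | Arm means | V |
|---|---|---|
| A: 0.5 SD, preoperative factor only | 0, 0, −0.5, −0.5 | 0.0625 |
| B: 0.5 SD for each factor | 0, −0.5, −0.5, −1 | 0.125 |
| C: 1.135 SD in any active arm | 0, −1.135, −1.135, −1.135 | 0.242 |
| D: 1.135 SD for each factor (extreme) | 0, −1.135, −1.135, −2.27 | 0.644 |

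**Step 3. Baseline predictor.** The pooled Pearson correlation is 0.3/√(1 + V). Power is from simulation (20,000 replicates), comparing pooled Spearman with Spearman on ranks centred within arm.

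| Scenario | 0.3/√(1 + V) | Simulated pooled rho | Power, pooled | Power, arm-adjusted |
|---|---|---|---|---|
| A | 0.291 | 0.28 | 83% | 84% |
| B | 0.283 | 0.27 | 81% | 84% |
| C | 0.269 | 0.26 | 77% | 84% |
| D | 0.234 | 0.22 | 64% | 84% |

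With the mg means of Step 1 and SDs 25/14/14/14 the result is close to C: about 76% against 83%. With no true correlation, the pooled test rejects in about 5% of runs in every scenario, so there are no false links here.

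**Step 4. Two postoperative measures with no within-arm link.** Let treatment shift the second measure by a fraction f of its effect on morphine. The pooled Pearson correlation is then fV/√((1 + V)(1 + f²V)). For scenario C with f = 1 this is 0.242/1.242 = 0.195; the simulated rho is 0.19.

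| Scenario | False positives pooled, f = 0.5 | f = 1 | Arm-adjusted |
|---|---|---|---|
| A | 6% | 9% | 5% |
| B | 9% | 20% | 5% |
| C | 18% | 50% | 5% |
| D | 69% | 99% | 5-6% |

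With no arm effect the pooled rate is 5%. With means 68/45/45/45, SDs 25/14/14/14 and a shift of 0.25-0.5 SD per etoricoxib component in the second measure, it is about 9-22%.

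**Step 5. CYP effect through etoricoxib only.** Three arms of four are exposed, so the pooled effect is 3/4 of the true one: 0.6 × 0.75 = 0.45 SD. Assuming 0.6 SD and 35% carriers (6,000 replicates), power is 37-56% pooled over four arms (56% with no arm effect, 37% in D) and 67-69% in the exposed arms with arm in the model. The false-positive rate stays at 5% in both.

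**The case against.** The strongest reply is that pooling is inferred. The association sentence lists test families; it neither pools the arms nor separates them. Collecting blood from everyone describes sampling, not an analysis set. A condensed article may leave stratification of exploratory analyses to the full plan. This stands as a limit on the point. However, the article does fix the methods for associations, and it puts treatment into the other analyses but not into these. A plan that follows the sentence literally has the problem.

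A reader might infer that the named tests are incapable of handling arm. They are not: partial Spearman and van Elteren tests are stratified forms of them, and all three can be run within arms.

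A reader might also infer that real sensory or genetic predictors would be hidden. Under a moderate arm effect the loss is 1-3 points of power. The 64% figure needs 1.135 SD for each factor added together, a spread that the article does not state; its 23 mg is a treatment-placebo difference from a cited study.

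On postoperative measures, the sensory prediction aim rests on preoperative testing, and repeated sensory and pain data go to a model that includes treatment. No correlation of postoperative sensory tests with morphine is expressly announced. The inflation is therefore conditional on such an analysis being run.

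On CYP, the gain comes almost entirely from the choice of population. In a separate run (20% carriers, 10 mg effect), a plain rank test in the exposed arms had power 0.686, and 0.701 with arm added. The Genetics section calls CYP2C9, CYP2C19 and CYP2D6 a minor fraction of etoricoxib metabolism, so the assumed effects may be generous. Its question, "have a possible connection with the outcome of postoperative pain management", is also broader than clearance. Making the exposed arms the main analysis is thus debatable.

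**Conclusion.** The point holds in a limited form: the association tests, as named, leave out a factor that the trial expects to move the outcome.

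- **Baseline sensory tests and genotype:** no bias and no false links; power falls from about 84% to 77-83% in scenarios A-C, given a within-arm correlation of 0.3.
- **Associations between two postoperative measures:** false-positive rates of about 6-50% in scenarios A-C against 5% adjusted, but only if such pairs are tested over pooled arms and etoricoxib shifts both.
- **CYP effects through etoricoxib clearance:** diluted to three quarters. This follows from the design, whereas the power figures rest on an assumed effect and carrier share. Adjustment for arm alone does not cure it. It does not apply to an opioid-related MDR1 effect, which can be present in all arms.

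The documents do not support the stronger reading that the planned associations are invalid as a whole. They are secondary and exploratory, and the primary factorial ANOVA is unaffected. Correcting the method is still worthwhile, because predictors and genetics are stated aims and the better analysis needs no new data.

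**What to change.** Amend the association sentence in Data Analysis, or settle the matter in the analysis plan, as follows:

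1. Run every association with morphine use or pain conditional on the two treatment factors (preoperative and postoperative etoricoxib). Use a regression or rank-based model with both factors, or arm-stratified (partial) Spearman and van Elteren tests.
2. For CYP genotypes, add a genotype-by-etoricoxib-exposure term, or report the three exposed arms with arm in the model as a supporting analysis.
3. Keep MDR1 in all patients, adjusted for arm.

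The cost is wording and some extra analysis code; all variables are already collected. The supporting CYP analysis would use about 108 × 3/4 = 81 patients.

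The interaction term has limited power. Its standard error is that of the exposed-arm effect times √((1/81 + 1/27)/(1/81)) = 2. For 0.6 SD and 35% carriers it is √(1/81 + 1/27)/√(0.35 × 0.65) = 0.222/0.477 = 0.466. Then z = 0.6/0.466 = 1.29, and power is roughly Φ(1.29 − 1.96) = 25%. It should therefore be reported as an estimate with its confidence interval, and a non-significant result should not be read as no interaction.
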